### Participant inclusion criteria

2.2

1.Confirmed to have persistent aPL, defined as positivity of one or two aPL, ie, LA, aCL, and/or aβ2GP1 antibodies (IgG and/or IgM) at >40 GPL (IgG phospholipid units) or MPL (IgM phospholipid units) units or >99th centile of normal, on 2 or more occasions at least 12 weeks apart.2.One or more of a) ischemic stroke; b) TIA with evidence of either acute or chronic ischemic injury on brain MRI—including diffusion-weighted imaging lesion(s), previous cortical or subcortical infarction(s), or WMHs—and diagnosed by a clinician with expertise in stroke; c) brain infarcts (territorial or subcortical) or WMHs of presumed vascular origin on brain MRI, with or without cognitive impairment; and an expert clinical opinion that anticoagulation is a reasonable treatment option (with aim of preventing ischemic brain injury).3.Body weight ≥ 50 kg and ≤135 kg.4.Adequate contraception (barrier or hormonal) in women, unless postmenopausal or sterilized.

There was no requirement for the participant’s diagnosis, as per inclusion criteria (1) and (2), to have been made within a certain timeframe prior to enrolment, ie, both *de novo* and established cases were considered. Furthermore, eligibility was not restricted according to the participant’s antithrombotic treatment (active/historical), if any, prerandomization.

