### Outcomes

2.5

The primary outcome is the rate of change in WMH volume (assessed on MRI—a surrogate marker of ischemic damage).

Secondary outcome measures, encompassing neuroradiological and clinical parameters of efficacy and safety, health economics, anticoagulation intensity, and exploratory outcomes including rivaroxaban pharmacokinetic (PK) modeling, are outlined in the Table.

**Table tbl1:** Secondary outcomes of trial.

A. Efficacy
1. Neuroradiological markers i) Rates of change in mean diffusivity (assessed on MR imaging) ii) Rates of change in mean fractional anisotropy (as a measure of microstructural white matter damage derived from diffusion tensor imaging) iii) Rates of change on T1-weighted volumetric images of total brain volume iv) Rates of changes on T1-weighted volumetric images of white matter hyperintensities v) Rates of change on T1-weighted volumetric images of grey matter volume vi) Total number of brain infarcts per person as well as the number of these events overall vii) Number of subcortical brain infarcts per person as well as the number of these events overall viii) Number of cortical brain infarcts per person as well as the number of these events overall
2. Clinical i) Vascular events a) Number of ischemic stroke or transient ischemic attacks per person as well as the number of these events overall b) Number of occlusive arterial events at other sites, including systemic embolism per person, as well as the number of these events overall c) Number of cerebral venous thrombosis per person as well as the number of these events overall d) Number of venous thromboemboli at other sites per person as well as the number of these events overall e) Number of microvascular thrombosis per person as well as the number of these events overall f) Number of superficial venous thrombosis per person as well as the number of these events overall ii) Death iii) Composite clinical outcomes a) The number of the composite of all thrombotic events: arterial, venous, microvascular, and death per person, as well as the number of these events overall b) The number of Major Adverse Cardiac and Cerebrovascular events per person, as well as the number of these events overall iv) Rate of change in cognitive function assessed by the Montreal Cognitive Assessment in conjunction with the Queen Square Cognitive Assessment score
B. Safety

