### Assignment of interventions (allocation and blinding)

2.9

Participants were randomized by site Principal Investigator/delegate via Sealed Envelope online randomization service, with minimization by SLE status. Due to the requirements of safe anticoagulant management, treatment allocation is not blinded during the study, except at the stage of outcome analysis (brain imaging, neurologic outcomes, bleeding, and recurrent thrombotic events).

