### Statistical methods for analyzing primary and secondary outcomes

2.11

The primary outcome will be analyzed using a linear mixed effects model to compare the mean rate of change in WMH volume over time between the two randomized groups. This will allow estimation of average slope in each group with respective 95% CIs, while allowing for variability between individuals within each group. Interparticipant clustering will be modeled by fitting a random intercept model, and measurement of differences in rates of WMH volume changes for each participant will be facilitated by introducing a random slope. The primary model will not include explanatory variables apart from the minimization variable. The fixed effects will include randomized groups only. We will restrict the sample to those who have completed the study and provided data for two MRI scans, as we do not feel that the assumptions of Missing At Random (MAR) or Missing Completely At Random (MCAR) are appropriate in this clinical context.

Further details are provided in the Supplementary File, including (i) methods for additional analyses (eg, subgroup and adjusted analyses) and (ii) definition of analysis population relating to protocol nonadherence and statistical methods to handle missing data.

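### The primary model uses baseline WMH volume only as the first response, not as an adjustment variable, and so gives up precision that depends on an unstated baseline–slope correlation

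*Protocol article*

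**What the plan says.** The Outcomes section (2.5) defines the endpoint: "The primary outcome is the rate of change in WMH volume (assessed on MRI—a surrogate marker of ischemic damage". Section 2.11 states the method: "The primary outcome will be analyzed using a linear mixed effects model to compare the mean rate of change in WMH volume over time". It adds a participant-level random intercept ("Interparticipant clustering will be modeled by fitting a random intercept model") and a random slope.

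On covariates, section 2.11 is explicit: "The primary model will not include explanatory variables apart from the minimization variable". It then says "The fixed effects will include randomized groups only". Section 2.9 identifies the minimization variable, since allocation was made "with minimization by SLE status". WMH burden plays no part in allocation.

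The analysis set consists of participants with both scans: "We will restrict the sample to those who have completed the study and provided data for two MRI scans". Every analysed participant therefore has a baseline WMH volume. Adjusted analyses are mentioned in section 2.11, but as additional analyses described in the Supplementary File, which is not at hand.

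**The concern.** A baseline measurement of the outcome is often the strongest predictor of later change, and here it is available for everyone analysed at no extra cost. The plan uses it as one of two response values. Whether that amounts to adjustment depends on how the baseline means are modelled. If each arm has its own baseline mean, the model subtracts baseline from follow-up and does nothing more. If arms share one baseline mean, as randomization justifies, the model also uses the association between baseline and change.

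The article does not impose a common baseline mean, and it names randomized group as a fixed effect. Its planned precision is that of an unadjusted comparison. In a trial of 40 participants whose expected 95% half-width already exceeds the noninferiority limit, a cheap source of precision should not be left out of the primary estimator without a reason.

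**Working it through.** **Inputs.** From section 2.7: at least 40 participants, slope SD 0.5, limit 0.25, expected 95% half-width ±0.32. From section 2.4: 1:1 allocation, so 20 per arm. That is a maximum if exactly 40 enrol, because participants without both scans are dropped. Assumed: r, the correlation between baseline WMH volume and slope, which is shown as a range because the article gives no value.

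**Step 1: reproduce the plan's figure.** The standard error of a difference between two arm means is 0.5 × √(2/20) = 0.158. Multiplying by t(0.975, 38 df) = 2.024 gives 0.320. The stated ±0.32 is therefore the half-width of an unadjusted two-arm comparison of slopes.

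**Step 2: what the mixed model estimates with two scans.** Data were simulated with 20 per arm and scans at 0 and 2 years, with an unstructured covariance for the two scans and 300 trials for each r.
- With free arm means at baseline, the slope contrast equalled the raw difference in annualised change to rounding error.
- With a common baseline mean, it equalled the ANCOVA estimate to rounding error.

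The SD of the estimate, unadjusted versus adjusted, was 0.152 vs 0.153 (r = 0), 0.154 vs 0.150 (r = 0.3) and 0.154 vs 0.137 (r = 0.5).

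**Step 3: size of the gain.** Adjustment multiplies the variance by 1 − r². The half-width becomes t(0.975, 37 df) × 0.5 × √(1 − r²) × √(2/20), with t = 2.026. Allowing for expected covariate imbalance multiplies this by √(1 + 1/36) = 1.014. Power is against 0.25 at one-sided 5% (normal approximation, no true difference); the article does not state the sidedness of its 10% alpha.

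| r | 1 − r² | 95% half-width | with imbalance allowance | power |
|---|---|---|---|---|
| unadjusted | 1 | 0.320 | – | 47.5% |
| 0 | 1 | 0.320 | 0.325 | 47.5% |
| 0.3 | 0.91 | 0.306 | 0.310 | 50.5% |
| 0.5 | 0.75 | 0.277 | 0.281 | 57.2% |
| 0.6 | 0.64 | 0.256 | 0.260 | 63.0% |
| 0.7 | 0.51 | 0.229 | 0.232 | 71.5% |

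The power column does not include the imbalance allowance.

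**Step 4: effect of a chance imbalance.** The standardised baseline difference between arms has SD √(2/20) = 0.316. An imbalance of d baseline SDs shifts the unadjusted slope difference by r × 0.5 × d.
- One standard error (d = 0.316): 0.3 × 0.5 × 0.316 = 0.047 at r = 0.3, and 0.5 × 0.5 × 0.316 = 0.079 at r = 0.5.
- d = 0.5: 0.5/0.316 = 1.58 standard errors, with two-sided probability 0.114. At r = 0.5 the shift is 0.5 × 0.5 × 0.5 = 0.125, which is half of 0.25.

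**Step 5: these are one effect, not two.** At r = 0.5 the unadjusted variance is 0.158² = 0.025. The imbalance component is 0.079² = 0.00625. The remainder, 0.01875, is 0.75 × 0.025, the adjusted variance. The possible shift is already inside the ±0.32, and adjustment removes it from there.

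**The case against.** The case for leaving the plan alone has real strength.

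- **Baseline is in the model.** It is the time-zero response, so a difference in baseline level is subtracted out of the slope. A reader might infer that baseline WMH is ignored, or that any baseline imbalance carries straight into the result. Neither is so; only the part acting through r remains.
- **The comparison is not biased.** A reader might infer that the unadjusted result would be misleading. Under randomization it is unbiased on average with valid coverage, and Step 5 shows that its interval already allows for chance imbalance. Selection through the completer restriction is a different issue.
- **The gain is conditional.** Nothing in the article supports a particular r. Up to about 0.3 the gain is small. The eligibility wording in section 2.2, "both *de novo* and established cases were considered", concerns when the diagnosis was made, so it does not show how widely baseline WMH volume will spread.
- **The shift is not as large as the limit.** The illustrative 0.125 is half of it and needs both r = 0.5 and an imbalance with an 11% chance.
- **The intended model is not settled.** Section 2.11 does not name time or group-by-time as fixed effects. If the model constrains baseline means to be equal, it already delivers the adjustment.
- **Adjusted analyses are planned.** Adjusting the primary analysis only for the minimization factor is a legitimate choice in a proof-of-principle trial.

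All of this limits the size and wording of the point. It does not remove it: the covariate set is fixed in the article, a common baseline mean is not stated, and an additional adjusted analysis does not improve the precision of the primary one.

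**Conclusion.** The point holds as one of efficiency. As described, and on the reading that arm means are free at baseline, the primary contrast is the unadjusted difference in mean change. Adjusting would reduce the 95% half-width by about 4% at r = 0.3 (0.306/0.320), 13% at r = 0.5 (0.277/0.320) and 28% at r = 0.7 (0.229/0.320). At r = 0 it would increase it by a little over 1% (0.325/0.320). That asymmetry favours adjusting even though r is unknown. The figures assume 20 analysed per arm, SD 0.5 and a linear relation between baseline and slope.

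A reader might hope that adjustment rescues the trial's precision. The figures do not support that: even at r = 0.6 the 95% half-width (0.256) exceeds 0.25. Forty participants reproduce for a difference of 0.4 at one-sided 5% and 80% power; the stated limit of 0.25 needs 100 on the same terms. That conflict in section 2.7 is a separate matter.

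**What to change.** Before unblinded outcome data are seen, specify one of two equivalent primary estimators:

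1. An ANCOVA of annualised WMH change (or of 24-month WMH volume, with the coefficient put on an annual scale) on randomized group, baseline WMH volume and SLE status.
2. A mixed model of the two scans with a common baseline mean across arms and an unstructured covariance, reporting the group-by-time contrast. To match the ANCOVA, SLE status must be allowed to affect both the baseline mean and the change.

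Fix the scale or transformation of baseline WMH volume in advance, rather than choosing it from the data. Do not add baseline as a covariate to a mixed model in which it is also a response row. Name time and group-by-time explicitly among the fixed effects. Keep the unadjusted difference in change as a sensitivity analysis.

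The cost is a change of wording in the analysis plan and one degree of freedom. No new data are needed. The downside is the loss of a little over 1% in precision if baseline volume turns out to be unrelated to slope.

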### Trial design, participants, interventions, and outcomes

2.1

The Rivaroxaban for stroke patients with APS (RISAPS) trial is a phase IIb prospective, randomized, controlled, noninferiority, open-label, proof-of-principle trial in adult patients with APS and previous ischemic stroke, TIA, or other ischemic brain manifestations. Eligible patients from participating centers in UK, after providing fully informed written consent, were enrolled and randomized 1:1 to either high-dose rivaroxaban 15 mg twice daily or high-intensity warfarin, target INR 3.5 (range, 3.0-4.0), the latter being regarded as standard of care in this study. The primary outcome for comparison of relative efficacy is the rate of change in brain WMH volume on magnetic resonance imaging (MRI), a surrogate marker of ischemic damage, between baseline and 24 months follow-up between these 2 treatment arms.

The study design was amended from phase II/III to phase IIb following revision of sample size target from 140 to 40 participants (minimum). This was necessitated by adverse recruitment factors, including in relation to the COVID-19 pandemic and decision to exclude triple-aPL-positive patients.

The official title of the trial is: Rivaroxaban vs Warfarin for Stroke Patients With Antiphospholipid Syndrome, With or Without SLE (RISAPS): a Randomised, Controlled, Open-label, Phase IIb, Non-inferiority Proof of Principle Trial.

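### The fixed-effects sentence for the primary model contradicts its own paragraph and, read literally, leaves no parameter for the difference in mean slopes

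*Protocol article*

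**What the plan says.** Section 2.1 of the protocol article defines the primary outcome as the rate of change in WMH volume "between baseline and 24 months follow-up between these 2 treatment arms". Section 2.7 places the noninferiority limit of 0.25 on the difference in mean annual slopes, with WMH volume as a percentage of brain volume.

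Section 2.11 then describes the primary analysis in five steps:

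- Purpose: a "linear mixed effects model to compare the mean rate of change in WMH volume over time between the two randomized groups".
- Output: "This will allow estimation of average slope in each group with respective 95% CIs".
- Random effects: a random intercept, and "measurement of differences in rates of WMH volume changes for each participant will be facilitated by introducing a random slope".
- Covariates: "The primary model will not include explanatory variables apart from the minimization variable". Section 2.9 identifies that variable as SLE status.
- Fixed effects: "The fixed effects will include randomized groups only".

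The analysis is restricted to participants who completed the study and "provided data for two MRI scans". No fixed time term or group-by-time term is named. Further details are referred to a Supplementary File that is not shown.

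**The concern.** When the outcome is WMH volume measured repeatedly, a difference between arms in mean rate of change is the group-by-time interaction. The last step excludes that term in so many words, because it says the fixed part contains randomized group and nothing else. It therefore contradicts the first two steps, which promise a slope per arm and a comparison of slopes. It also contradicts the fourth: a binary covariate that is in the model and is not a random effect must be a fixed effect.

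At stake is the quantity on which noninferiority is judged. A reader cannot tell from the text which coefficient will be set against the limit. In an open-label trial, an unclear primary model also leaves room to settle the time and SLE terms after the data have been seen.

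**Working it through.** **1. The scale of the plan's own figures.** Inputs from section 2.7: slope SD 0.5, 40 participants, 80% power, alpha 10%, a difference of 0.4% per year. Allocation is 1:1 (section 2.1), so 20 per arm.

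- SE of a difference in mean slopes: 0.5 × √(2/20) = 0.158.
- 95% half-width: t(0.975, 38 df) × 0.158 = 2.024 × 0.158 = 0.320. This is the stated ±0.32.
- n per arm = 2 × (1.645 + 0.842)² × 0.5² / 0.4² = 19.3, rounded up to 20. This is the stated 40, with alpha taken as one-sided 5% (two-sided 10%).

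Both figures are on the scale of a difference in mean slopes, so that is the intended estimand.

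**2. The literal model.** With g = 0 or 1 for arm and t in years:

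Y = β0 + β1·g + u0 + u1·t + e, where u0, u1 and e have mean zero.

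The mean of Y is β0 + β1·g at every t. The implied average slope is zero in both arms, and no parameter is a slope difference. β1 is a difference in WMH level, in % of brain volume.

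**3. The model the paragraph needs.**

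Y = β0 + β1·g + β2·t + β3·g·t + (SLE) + u0 + u1·t + e.

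The average slopes are β2 and β2 + β3. The treatment effect is β3, in % of brain volume per year.

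**4. What the literal group coefficient measures.** For scans at 0 and 2 years, generalised least squares gives a weighted mean of the level differences at the two scans. With uncorrelated intercept and slope, the weight on the 24-month scan is w = σe² / (4σ1² + 2σe²), where σe is the residual SD and σ1 the random-slope SD. Taking σe = 0.1 (assumed) and σ1 = 1.17, w = 0.01 / (5.48 + 0.02) = 0.0018. A true slope difference of 0.5 per year, which is 1.0 over two years, then adds only about 0.002 to the coefficient. A non-zero intercept-slope covariance would change w, but the result would still be a difference in level.

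**5. Simulation check.** 150 trials per scenario, 20 per arm, scans at 0 and 2 years, mean slope 0.8, slope SD 0.5. Assumed, not in the document: baseline mean 3, baseline SD 2.0, residual SD 0.1 (held fixed), intercept-slope correlation 0. SLE status was not simulated.

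| Fixed effects | True slope difference | Coefficient | Mean SE | Estimated random-slope SD |
|---|---|---|---|---|
| Group only | 0 | -0.04 (group) | 0.61 | 0.94 |
| Group only | 0.5 | 0.07 (group) | 0.61 | 1.17 |
| Group, time, group-by-time | 0 | -0.00 (interaction) | 0.153 | 0.48 |
| Group, time, group-by-time | 0.5 | 0.47 (interaction) | 0.153 | 0.48 |

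The full model recovers the difference. Its 0.47 lies about two Monte Carlo errors from 0.5 (0.161/√150 = 0.013), and its SE is close to the 0.158 of step 1. The group-only coefficient shows no response to the slope difference. The mean growth goes into the random-slope SD instead: √(0.5² + 0.8²) = 0.94 with no slope difference, and √(0.5² + (0.8² + 1.3²)/2) = 1.19 with a difference of 0.5.

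**6. Dependence on the baseline SD.** The literal coefficient has an SE of about baseline SD × √(2/20). Set against 0.158:

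| Assumed baseline SD | SE | Ratio |
|---|---|---|
| 0.5 | 0.158 | 1 |
| 1.0 | 0.316 | 2 |
| 2.0 | 0.632 | 4 |

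**7. Identifiability.** Two scans at common times give a 2×2 within-participant covariance matrix, which has three free elements. A random intercept, a random slope, their covariance and a residual variance are four parameters. They cannot all be estimated, which is why the residual SD was held fixed in step 5.

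**The case against.** The strongest defence is that the paragraph must be read as a whole. A random slope requires time in the model, and an average slope per arm with a confidence interval requires fixed time and group-by-time terms. On this view the last two steps only list explanatory variables (treatment and the minimization factor, no others), and time is taken for granted as the axis of a slope model. The article also condenses a fuller protocol, and the exact model formula is commonly left to the SAP.

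Most of this stands. A reader might infer that the model has no slope term and that the trial cannot estimate its primary comparison. The document does not support that: it names a random slope and states the slope comparison as the aim. Nor does it support saying that SLE status will be left out, since the preceding sentence admits it.

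Two things remain. First, the sentence does not omit a detail; it states an exclusion, and the exclusion is wrong for the stated aim. Second, the charitable reading still has to set the word *only* aside twice, for time and for SLE status. The Supplementary File is described as covering, among other things, additional analyses, the analysis population and missing data. It may also give the primary model, but that cannot be confirmed.

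Another reading is that the outcome is each participant's own rate of change. Group alone would then give the slope difference. But each participant would contribute one value, and the random intercept and random slope would have no role.

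**Conclusion.** The fixed-effects sentence is mis-stated and contradicts both the purpose of its own paragraph and the sentence before it. Read literally, no fixed parameter corresponds to the difference in mean slopes to which the 0.25 limit applies. That conclusion is algebraic and rests on no assumed value.

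The size of any precision loss is not established. The fourfold SE that a reader might take from a simulation is simply the assumed baseline SD of 2.0 divided by the slope SD of 0.5; at a baseline SD of 0.5 there would be no loss. Nor can it be said that the group-only model will actually be fitted, because intent points the other way and the full specification is not shown.

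Severity: should-fix. The sentence should be corrected, or reconciled with the SAP, before the primary analysis is run.

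**What to change.** Delete the restriction to randomized groups and state the model in one of two ways.

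- **Mixed model.** Fixed effects: randomized group, time (years since the baseline scan), group-by-time and SLE status. The treatment effect is the group-by-time coefficient, rivaroxaban minus warfarin, in % of brain volume per year, and it is compared with the noninferiority limit. With two scans at common times, also state a covariance structure that can be estimated, such as an unstructured 2×2 matrix.
- **Change regression.** Regress annualised WMH change on group and SLE status. With two scans per completer this is simpler and fully identifiable.

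The two are not interchangeable as listed. With a common scan interval, the change regression corresponds to the mixed model with a group main effect and with SLE-by-time added. It does not correspond to a model without the group main effect, which would constrain the arms to equal baseline means. SLE-by-time is optional in the mixed model, but the choice should be fixed in advance.

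The cost is one sentence in the protocol and a matching line in the SAP. It needs no new data and leaves the target of 40 unchanged.

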### Interventions

2.4

Participants were randomized in a 1:1 ratio to either high-dose rivaroxaban 15 mg twice daily (film-coated tablets to be taken orally with food) or high-intensity warfarin, target INR 3.5 (range, 3.0-4.0) for 24 months. Participants on warfarin require INR monitoring by an appropriate anticoagulation clinic in line with usual practice. Adherence to trial medication is assessed by completion of the Medication Adherence Rating Scale (MARS) at each follow-up visit. In addition, for participants on warfarin, INR documentation is reviewed.

The Supplementary File provides further information relating to interventions, including safety processes to mitigate bleeding risk and criteria for anticoagulation review ± modification during trial (including bleeding and thrombosis, weight change, and moderate/severe renal impairment).

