### Sample size

2.7

The study sample size target was a minimum of 40 participants. RISAPS is a noninferiority trial. Previous research has suggested that noninferiority margin should be half the SD of the primary outcome from historical studies. Accordingly, sample size calculations are based on a study by Benjamin et al. [29]. This used data from the prospective St George’s Cognition and Neuroimaging in Stroke study of patients with symptomatic lacunar stroke and confluent leukoaraiosis (*n* = 121) to determine sensitivity of MRI to change in small vessel disease (SVD) and calculate sample size estimates for a clinical trial. The mean slope (ie, annual rate of change of WMH volume expressed as a percentage of brain volume) was an increase of 0.8% (95% credible interval, 0.67%-0.95%), with a SD of 0.5. To perform a sample size calculation for RISAPS, we have therefore chosen a noninferiority limit of 0.25, ie, the smallest difference in mean slopes between the two groups that would lead us to conclude inferiority. Our noninferiority limit corresponds to half the between-patient variability in slopes. With the planned sample size of 40, we would be able to establish noninferiority based on approximately 50% of this change (a mean increase of 0.4% per year). We have applied a more liberal type I error rate (alpha, falsely declaring a difference when one does not exist) of 10%, which is in line with most phase IIb trials, given that they are not confirmatory in nature.

In practice, 95% CI for WMH volume change will be ±0.32, given the expected SD of 0.5, due to the use of fully observed data as opposed to the formal sample calculation, which adjusted for power of 80%.

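### The reason given for the completers-only primary analysis does not support it: that analysis needs a stricter missing-data assumption than the MAR assumption the protocol rejects

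*Protocol article*

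**What the plan says.** Section 2.11 (Statistical methods) describes the main comparison in these terms: "analyzed using a linear mixed effects model to compare the mean rate of change in WMH volume over time between the two randomized groups", with a random intercept and a random slope. On covariates it says: "The primary model will not include explanatory variables apart from the minimization variable". Section 2.9 identifies that variable as SLE status.

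The analysis set is fixed in the same section: "We will restrict the sample to those who have completed the study and provided data for two MRI scans". The reason follows directly: "we do not feel that the assumptions of Missing At Random (MAR) or Missing Completely At Random (MCAR) are appropriate in this clinical context".

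Section 2.11 then refers to the Supplementary File, which is not shown, for the "definition of analysis population relating to protocol nonadherence and statistical methods to handle missing data".

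Section 2.7 (Sample size) states "RISAPS is a noninferiority trial". It sets a limit of 0.25 on the difference in annual slopes, assumes an SD of 0.5, targets at least 40 participants, and gives a 95% CI half-width of 0.32 that presumes every participant is observed.

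**The concern.** Rejecting both MAR and MCAR amounts to saying that whether a second scan exists may depend on the unseen change in WMH volume. Leaving out people without that scan does not avoid the difficulty. It carries an assumption of its own, that those left in represent those left out within each arm and SLE stratum. The stated reason therefore contradicts the chosen method.

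The primary noninferiority conclusion is at stake. Treatment is open-label, so loss could differ between arms. If one arm loses more of its fast progressors, its mean slope among completers looks better than its mean slope among all those randomized to it. With about 20 participants per arm, a few people can matter.

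**Working it through.** **Inputs from the protocol article.** Section 2.7: SD of annual slope 0.5, limit 0.25, 40 participants, a difference of 0.4 that 40 participants can exclude, alpha 10%, power 80%, half-width 0.32. Section 2.4: 1:1 allocation, so 20 per arm. Dropout shares and the excess slope of non-completers are **not** given; those below are assumptions.

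**Step 1: the plan's own figures.**
- Sample size, reading 10% as two-sided: n per arm = 2(1.645 + 0.842)² × 0.5² / 0.4² = 19.3, rounded up to 20, so 40 in total. This reproduces.
- Half-width: t(0.975, 38 df) × 0.5 × √(2/20) = 2.024 × 0.158 = 0.320. This reproduces.

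The stated precision thus needs all 40 in the analysis. With 10% lost (18 per arm) the half-width is 0.339.

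**Step 2: what the completers analysis assumes.** Within an arm, let f be the share without a second scan and e the amount by which their mean slope exceeds that of completers. Then

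mean slope of all randomized = mean slope of completers + f × e.

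The completers' difference between arms equals the difference in all randomized only if f × e is the same in both arms. Unless errors happen to cancel, this means e = 0 given the model terms: having the second scan is unrelated to slope given arm and SLE status (covariate-dependent MCAR). MAR is weaker, because it also lets missingness depend on observed data such as baseline WMH volume. A likelihood analysis that keeps baseline-only participants can use that information; a completers analysis discards it. If missingness depends on the unseen slope itself, e is not zero and the completers analysis is biased.

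**Step 3: possible size.** Suppose completers progress equally in both arms and e is the same in both arms. The difference hidden by the analysis (rivaroxaban minus warfarin) is (f_R − f_W) × e.

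| Loss, rivaroxaban vs warfarin | e = 0.5 (1 SD) | e = 1.0 (2 SD) | Share of the 0.25 limit |
|---|---|---|---|
| 15% vs 5% (3 vs 1 of 20) | 0.05 | 0.10 | 20% to 40% |
| 20% vs 5% (4 vs 1 of 20) | 0.075 | 0.15 | 30% to 60% |
| 10% vs 10% | 0 | 0 | 0% |
| 5% vs 15% | −0.05 | −0.10 | −20% to −40% |
| 5% vs 20% | −0.075 | −0.15 | −30% to −60% |

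A positive entry means that rivaroxaban looks better than it is. A negative entry means that the analysis works against noninferiority.

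**Step 4: an extreme pattern, as an outer bound.** Simulation with 10,000 trials per scenario, 20 per arm, SD 0.5, one-sided 0.05, and the true difference equal to the limit (0.25 or 0.4; results are nearly the same). If the fastest progressors among 20 on rivaroxaban, and nobody on warfarin, lack a second scan, the false noninferiority rate is about 10% for one person missing, 15% for two, 22% to 23% for three and 29% to 30% for four, against a nominal 5%. Random loss of two leaves it at about 5%. Losing the two fastest in both arms gives about 7%, with almost no bias.

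**The case against.** **Treatment failures.** A reader might infer that the restriction removes the treatment failures. The document does not support that. Section 2.11 excludes for non-completion or a missing scan, not for an event or a change of treatment. Section 2.4 provides "criteria for anticoagulation review ± modification during trial (including bleeding and thrombosis, weight change, and moderate/severe renal impairment", so a participant with a non-fatal event may stay, be rescanned and be analysed. Only those who die or leave before the second scan are certainly removed. Strokes, deaths and bleeds are also counted as secondary outcomes.

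**Early leavers with a scan.** A reader might also infer that people rescanned before leaving early are thrown away. Read literally, the completion requirement would do so, but the article describes no early-exit scan and the schedule figure is not shown. That group may be empty.

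**Direction.** A reader might infer that the bias must favour noninferiority. It does so only if rivaroxaban loses more fast progressors. It reverses if warfarin does, and largely cancels if selective loss is similar.

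**The supplement.** The Supplementary File may already hold sensitivity analyses, so the absence of a tipping-point analysis from the article is no fault. This objection stands. It does not rescue the primary set or its rationale, which the article states outright.

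**Phase and target population.** The trial is a small, non-confirmatory phase IIb study, which lowers the stakes but does not make the reasoning valid. One could also argue that the target is deliberately the slope among completers. The article does not say so, and a group selected after randomization would not carry the randomized comparison.

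**Conclusion.** The point holds in this form: the rationale in section 2.11 does not justify the completers-only primary set, because that set is unbiased for all randomized participants only under an assumption stricter than the one rejected. This follows from the text and needs no assumed figures.

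The consequence cannot be sized from the document. With excess slopes of 0.5 to 1.0 %/year among non-completers, and losses differing by 10 to 15 percentage points, the distortion is 0.05 to 0.15 in either direction, or 20% to 60% of the 0.25 limit. That could change a noninferiority conclusion, but it rests on assumed loss and assumed excess.

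**What to change.** 1. Delete the MAR/MCAR justification.
2. Define the primary set as all randomized participants with a baseline scan, analysed by allocation, using any available follow-up scan at its actual date whether or not the study or treatment was completed.
3. State the primary missingness assumption, for example MAR given arm and SLE status with the baseline volume kept in the model as an observed outcome. This is delta = 0, where delta is the added annual slope assumed for those without a follow-up scan.
4. State how deaths before the second scan are handled.
5. Pair the primary result with a delta-adjusted (MNAR) tipping-point analysis that varies delta separately in each arm, for example over 0, 0.25, 0.5 and 1.0 %/year, and report where noninferiority is lost. This step is essential: baseline-only participants carry little information on slope, so including them under MAR does not settle the matter alone.
6. Keep the two-scan completers analysis as a sensitivity analysis, and report missing scans and reasons by arm.
7. If the Supplementary File already contains such analyses, bring section 2.11 into line with it.

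Make the change before anyone responsible for the analysis has access to comparative data, and record that this was so. The cost is modest analysis work and a slightly wider interval; no new scans or participants are needed.
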